## Abstract

**Background:**

Preterm birth is associated with significant mortality and morbidity for mothers and babies. Women are identified as high risk for preterm birth based on either previous medical/pregnancy history or on ultrasound assessment of the cervix. Women identified as high risk can be offered a cervical cerclage (a purse string stitch) around the cervix (neck of the womb) to reduce the risk of preterm birth. In women who have a cervical cerclage, the procedure can be performed using either a monofilament (single-stranded) or braided (woven) suture material. Both suture materials are routinely used for cervical cerclage and there is uncertainty as to which is superior.

**Methods:**

A multicentre, open, randomised controlled superiority trial of 2050 women presenting at obstetric units, deemed to be at risk of preterm birth and already scheduled to have a cervical cerclage as part of their standard care. Inclusion criteria include singleton pregnancies and an indication for cervical cerclage for either a history of three or more previous mid-trimester losses or premature births (≤ 28 weeks), insertion of cervical sutures in previous pregnancies, a history of mid trimester loss or premature birth with a (current) shortened (≤ 25 mm) cervix, or women whom clinicians deem to be at risk of preterm birth either by history or the results of an ultrasound scan. Exclusion criteria include women who have taken part in C-STICH previously, are aged less than 18 years old at the time of presentation, require a rescue cerclage, and are unwilling or unable to give informed consent and in whom a cerclage will be placed by any route other than vaginally (e.g. via an abdominal route). Following informed consent, women are randomised on a 1:1 basis to either monofilament or braided suture, by minimisation. The primary outcome is pregnancy loss (miscarriage and perinatal mortality, including any stillbirth or neonatal death in the first week of life), and secondary outcomes include the core outcome set for preterm birth trials.

**Discussion:**

Optimising established interventions to prevent preterm birth is important in reducing perinatal mortality rates.

**Trial registration:**

ISRCTN 15373349. Registered before recruitment on 03 December 2014 prior to first recruit.

## Administrative information

Note: the numbers in curly brackets in this protocol refer to SPIRIT checklist item numbers. The order of the items has been modified to group similar items (see http://www.equator-network.org/reporting-guidelines/spirit-2013-statement-defining-standard-protocol-items-for-clinical-trials/).

## Introduction

### Background and rationale {6a}

Preterm birth (PTB) is one of the major global challenges in obstetrics and neonatology. An early birth puts survivors at risk of serious long-term disabilities and these outcomes pose a significant burden on parents as well as having economic implications on health services. Second trimester miscarriage and preterm birth form a continuum with the underlying cause often multifactorial and complex [1]. Cervical weakness is one cause of late miscarriage and preterm birth; this can be treated by a cervical cerclage.

A cervical cerclage can be performed either with a monofilament or braided suture material; both sutures are routinely used by clinicians [2]. A monofilament suture may be superior at preventing miscarriage, stillbirth and neonatal death through the prevention of early delivery [3].

## Objectives {7}

### Primary objective

To examine the effect of using monofilament suture material compared with braided suture material on pregnancy loss rate in women deemed to be at risk of an insufficient cervix and treated with a cervical cerclage.

### Secondary objectives

To assess the effect of suture material on other pregnancy and neonatal outcomes.To explore the variation in treatment effect between McDonald’s and Shirodkar’s cerclage, especially with reference to bladder dissection.To explore the variation in treatment effect between the different indications for cerclage.

## Trial design {8}

C-STICH is a multi-centre, parallel-group randomised controlled superiority trial, open to all maternity sites across the UK. Women are potentially eligible for C-STICH if they are attending antenatal clinics or admitted to obstetric wards in which the reviewing clinician believes that the placement of a cervical cerclage is the most appropriate treatment to prevent a miscarriage or preterm birth. Women will be invited to take part in the C-STICH trial after the decision is made to perform a cervical cerclage procedure providing that they meet the eligibility criteria detailed below.

## Methods: participants, interventions, and outcomes

### Study setting {9}

The trial is being open to all NHS maternity sites across the UK. A full list of trial sites can be obtained by contacting the Birmingham Clinical Trials Unit.

### Eligibility criteria {10}

Women are eligible if they are undergoing a cervical cerclage as part of their standard care.

#### Inclusion

Singleton pregnancyIndication for cervical cerclage for either:▪ A history of three or more previous midterm losses or premature births (≤ 28 weeks), OR▪ Insertion of cervical sutures in previous pregnancies, OR▪ A history of mid-trimester loss or premature birth with a (current) shortened (≤ 25 mm) cervix, OR▪ Women whom clinicians deem to be at risk of preterm birth either by history or the results of an ultrasound scan

#### Exclusion

Women who have taken part in C-STICH previouslyWomen aged less than 18 years old at the time of presentationThose with a multiple pregnancyThose requiring a rescue cerclage*Women who are unwilling or unable to give informed consentThose in whom a cerclage will be placed by any route other than vaginally (e.g. via an abdominal route)Immediate need for insertion of a suture**Women who have membranes that have ruptured or are surfacing***

*For study purposes, rescue cerclage is defined as emergency cerclage where sutures are inserted in women who have had their preterm labours (e.g. uterine contractions, progressive cervical dilatation, bulging membranes) sufficiently halted by tocolysis or other means between 15 and 28 weeks.

**Immediate need for insertion of a suture should not be delayed by the trial (thus, if giving information about the trial and waiting for the participant to decide upon whether or not she wants to participate will delay the insertion of an urgently needed suture, then treatment should go ahead and the woman should be excluded from the trial).

***Women with membranes that are ruptured or bulging through the external os are considered to be undergoing a rescue cerclage and be excluded from trial participation.

If a woman is screened but is not eligible for the trial, either due to a preference for a particular suture type, a contraindication to the trial, a pathological reason, or consent for randomisation is not given, an anonymous record of the case should be kept in the screening log. The screening log will collect initials, age group, ethnic group, and the reason each patient is not eligible to participate in the trial. Women who consent and are subsequently found to be ineligible should also be noted. The screening log should be kept in the site file and a copy sent to the C-STICH Trial Office on a monthly basis. Members of the trial co-ordination team will be unable to identify women based on the information provided. This screening log information will inform updates to the funder regarding recruitment targets for C-STICH Trial.

The clinician performing the cervical cerclage should be competent to perform the procedure and should routinely perform cervical cerclages as part of their standard practice.

### Who will take informed consent? {26a}

Potentially eligible women will be identified in antenatal clinics, outpatient departments, and obstetric wards and invited to join the trial after a decision is made to undertake a cervical cerclage.

#### Approaching potential participants for consent

Potential participants will only be approached by suitably qualified and experienced personnel who are recorded on the delegation log.

#### Obtaining consent

All women who are referred to secondary care for cervical cerclage should be considered potentially eligible and should be screened prior to their antenatal appointment by the designated C-STICH staff member in each centre. The obstetrician who will be providing the woman’s clinical care and performing the procedure will discuss preventative options and establish eligibility based on history and preferences.

The indication for the cerclage should be discussed before the trial is introduced. The trial should then be introduced by a suitable qualified staff member who is delegated to discuss the trial and recorded on the delegation log to do so. A Patient Information Sheet (PIS) should be given to the women. Consent should be informed and voluntary with time for questions and reflection. Adequate time should be allowed for consideration of participation in the trial before the cerclage procedure is undertaken. There is no pre-agreed specified time to consent.

Consent to participate in C-STICH will be sought by appropriately qualified staff who are both GCP trained and designated by the Principal Investigator to conduct informed consent procedures. Women will be asked to confirm their consent to participate in the C-STICH trial by initialling the appropriate boxes on the consent form and signing the form in the presence of the person taking consent.

A copy should be given to the women: one to be kept in the patient notes, the original should be kept in the local site file, and one copy sent to the C-STICH Trial Office at the University of Birmingham Clinical Trials Unit. The date the informed consent discussion took place should be recorded in the participant’s medical notes and the version number of the PIS provided to the participant.

Following consent, the woman’s GP should be notified using the study template letter.

### Additional consent provisions for collection and use of participant data and biological specimens {26b}

Routine microbiology samples, i.e. a high vaginal swab and the removed suture thread, will be collected for microbiology analysis. Consent for sample collection is included in the trial consent. Samples will be delivered to each participating hospital’s local diagnostic microbiology laboratory where they will be processed in accordance with local standard operating procedures and details of microorganisms cultured will be recorded. In laboratories which do not routinely process suture materials, they will be asked to place the suture in 3–5 ml of sterile 0.9% saline. After sonication or vigorous vortexing, 0.1-ml volumes should be cultured on appropriate agar plates for culture of aerobic and anaerobic bacteria and fungi.

### Interventions

#### Explanation for the choice of comparators {6b}

Following randomisation, a cerclage will be placed using either a monofilament or braided suture. Both types of suture used in C-STICH are standard surgical materials already in use. The suture material used must be CE marked for this purpose. The MHRA have confirmed that C-STICH is not classed as a device trial.

If randomised to the comparator braided group, the cervical cerclage should be performed using any appropriate braided suture type. There are different brands of each suture material and whilst the trial does not specify which brand a surgeon should use, the use of Mersilene® is encouraged in the braided group in order to standardise the suture types as far as possible. Mersilene® is a nonabsorbable, braided, sterile surgical suture composed of poly-ethylene terephthalate.

#### Intervention description {11a}

If randomsied to the intervention group, the cervical cerclage should be performed using a monofilament suture type. To standardise the intervention group as far as possible, Ethilon, a nonabsorbable, monofilament, sterile surgical suture composed of the long-chain aliphatic polymers Nylon 6 and Nylon 6,6 is recommended.

#### Criteria for discontinuing or modifying allocated interventions {11b}

Once a cervical cerclage is placed using the allocated suture thread, this cannot be modified or discontinued.

#### Strategies to improve adherence to interventions {11c}

To ensure adherence to the allocated suture material an email will be sent to all trial staff at the randomising centre detailing the allocation. We also recommend the allocated suture material being kept with the maternal medical records following allocation before insertion.

#### Relevant concomitant care permitted or prohibited during the trial {11d}

##### Cerclage technique

The technique of suture insertion (i.e. with or without bladder dissection) will be at the surgeon’s discretion and may include an additional occlusion stitch to close the external os. Should an additional occlusion stitch be used, we request that the same suture type as the randomised allocation be used. Technique of suture insertion will be included in the minimisation algorithm to ensure balance in treatment allocation for those who do and do not have a bladder dissection.

##### Other treatments

Apart from the suture material used during the cervical cerclage, all other aspects of the surgical procedure are at the discretion of the surgeon performing the procedure. Ongoing preterm birth prevention management, e.g. progesterone, antibiotics, and tocolytics, will be at the discretion of the clinician providing care and can all be used as required. Intention to commence progesterone will be included in the minimisation algorithm.

In rare instances, a second cervical cerclage may be required later in the pregnancy. In this case, the participant cannot be randomised a second time but should ideally be treated with the same suture material used in the initial cerclage.

The pregnancy should be managed as per current usual practice for women with a cervical cerclage, with no other special treatments, no special investigations, and no extra follow-up visits outside those required clinically are required for trial participation.

### Provisions for post-trial care {30}

There is no anticipated additional harm for women participating in C-STICH; both suture threads are routinely used in clinical practice.

### Outcomes {12}

C-STICH collects all the outcomes detailed in the core outcome set for preterm birth [4]. The primary outcome measure is pregnancy loss (miscarriage and perinatal mortality, including any stillbirth or neonatal death in the first week of life). A key secondary outcome in the C-STICH trial is time from conception to pregnancy end (any reason). Other maternal and foetal secondary outcomes include:

#### Maternal

Miscarriage and previable neonatal death (defined as delivery <24 weeks)Stillbirth (defined as intrauterine death ≥24 weeks)Gestation at delivery (in live births ≥ 24 weeks)Gestational age at delivery (in live births ≥ 24 weeks)Gestational age <28/<32/<37 weeks at delivery (in live births ≥24 weeks)Time from conception to onset of spontaneous vaginal delivery (in live births ≥24 weeks)Sepsis (at any time in pregnancy and until 7 days postnatal)Preterm pre-labour rupture of membranes (PPROM)Mode of initiation of labour (spontaneous or induced)Mode of delivery (vaginal, operative vaginal or caesarean)Cerclage placement complications (cervical laceration/bleeding from cervix/ruptured membranes/bladder injury)Cerclage removal complications (cervical tears/need for anaesthetic/difficult to remove)Other maternal complications: vaginal bleeding/steroid use/chorioamnionitis/maternal pyrexia of 38°C (intrapartum/postnatal)/ admission to HDU or ITU (pre/post-delivery)Serious adverse events

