#### Neonatal

Early neonatal death (defined as a death within 7 days after delivery)Late neonatal death (defined as a death beyond 7 days and before 28 days after delivery)Birth weight adjusted for gestational age and sex (in live births ≥24 weeks)Small for gestational age and sex (<10th centile, in live births ≥24 weeks)Resuscitation at birth/additional care required (SCBU/NICU/HDU/transitional)/length of stay in additional care (in live births ≥24 weeks)Antibiotics within 72 h/sepsis (clinically diagnosed/proven) (in live births ≥24 weeks)Early neurodevelopmental morbidity (severe abnormality on cranial ultrasound scan) (in live births ≥24 weeks)Respiratory support (ventilation/CPAP)/days on respiratory support (in live births ≥24 weeks)Supplementary oxygen requirements at 36 weeks post menstrual age(in live pre-term births ≥24 weeks, <36 weeks)Necrotising enterocolitis (Bell’s stage 2 or 3) (live pre-term births ≥24 weeks, <37 weeks)Retinopathy of prematurity requiring laser treatment/disabilities/congenital abnormalities (live pre-term births ≥24 weeks, <37 weeks)Serious adverse events

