## Statistical methods

### Statistical methods for primary and secondary outcomes {20a}

#### Statistical analysis

A separate statistical analysis plan for the quantitative analysis of the C-STICH study will provide a detailed description of the planned statistical analyses. A brief outline is given below. All analyses will be by intention to treat. Every attempt will be made to collect pregnancy outcome data on all women and it is anticipated that missing data will be minimal. Women with missing primary outcome data will not be included in the first instance.

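### Preterm-birth thresholds are compared only in live births from 24 weeks, and three neonatal items only in preterm live births, so treatment helps decide who is compared

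*Protocol article*

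**What the plan says.** In the Protocol article, Outcomes {12}, the maternal list gives "Gestational age at delivery (in live births ≥ 24 weeks" and "Gestational age <28/<32/<37 weeks at delivery (in live births ≥24 weeks". The events that take a pregnancy out of that denominator are listed separately: "Miscarriage and previable neonatal death (defined as delivery <24 weeks" and "Stillbirth (defined as intrauterine death ≥24 weeks".

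Most of the neonatal list carries the same restriction, for example "Respiratory support (ventilation/CPAP)/days on respiratory support (in live births ≥24 weeks". Three items are narrowed further. Oxygen at 36 weeks is taken "in live pre-term births ≥24 weeks, <36 weeks", necrotising enterocolitis is limited to births before 37 weeks, and so is "Retinopathy of prematurity requiring laser treatment/disabilities/congenital abnormalities (live pre-term births ≥24 weeks, <37 weeks".

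The section on additional analyses {20b} analyses binary secondary outcomes in the same way as the primary outcome, so these subsets receive adjusted between-arm relative risks. No version of the thresholds in all randomised women is stated.

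**The concern.** Background {6a} expects monofilament to avert miscarriage, stillbirth and neonatal death by preventing early delivery, and the primary outcome counts those losses. Membership of the live-birth subset is therefore an outcome of treatment.

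The same section treats second-trimester miscarriage and preterm birth as one continuum. A pregnancy saved from loss at 22 weeks may well deliver alive at 26 weeks. In the planned analysis that woman enters the denominator of the better arm as an event before 28 weeks, while her counterpart in the other arm, who miscarried, is not counted at all.

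The preterm-only denominators are more exposed, because being born preterm is itself something the suture may change. Babies can move into the subset from loss and out of it to term, so the direction of bias there cannot be read off in advance. For disabilities and congenital abnormalities the restriction also discards term babies, in whom these events can occur.

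At stake is whether the secondary results on prematurity and its complications can be read as effects of the suture.

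**Working it through.** **The plan's own figures (Sample size {14}).** With pooled variance and two-sided 0.05 (sidedness is not stated, so assumed), n per arm = [1.96√(2p̄q̄) + 1.2816√(p₁q₁ + p₂q₂)]² / (p₁ − p₂)².

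- 19% v 11.2% at 90% power: 441 per arm, 882 in total; 882/0.975 = 905 with 2.5% attrition. The stated 900 is reproduced closely.
- For 2050 no revised event rate is given. Solving with p₂ = 0.59 p₁ gives 9.0% v 5.31% (2048 without attrition), or about 9.2% if 2.5% attrition is allowed. I use 9.0%.

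**Inputs to the illustration**

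- Braided loss 9.0% (back-solved); risk ratio 0.59 (from the protocol's 41% reduction).
- Assumed: 80% of losses are before 24 weeks or stillbirths and leave the denominator, all of them ending before 28 weeks. The other 20% are early neonatal deaths after live birth at 24 weeks or later, which stay in it.
- Assumed: live births at 24 to 27 weeks are v = 5% of braided women.
- Assumed: a share f = 50% of rescued pregnancies is born alive at 24 to 27 weeks.

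**Calculation**

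- Leaving the denominator: braided 0.09 × 0.8 = 0.0720; monofilament 0.0531 × 0.8 = 0.0425.
- Rescued: 0.0720 − 0.0425 = 0.0295, of which half (0.0148) are born at 24 to 27 weeks.
- Planned (live births ≥24 weeks): braided 0.05/0.928 = 5.4%; monofilament (0.05 + 0.0148)/0.9575 = 6.8%. **Risk ratio 1.26.**
- All randomised, pregnancy ended before 28 weeks: braided 0.05 + 0.0720 = 12.2%; monofilament 0.0648 + 0.0425 = 10.7%. **Risk ratio 0.88.**

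**When it reverses.** If other births are unchanged, the planned proportion rises whenever f exceeds the braided proportion in the subset, here 5.4%.

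| Variation on the base case | Planned RR | All-randomised RR |
|---|---|---|
| Base case | 1.26 | 0.88 |
| No rescued pregnancy born at 24 to 27 weeks (f = 0) | 0.97 | 0.76 |
| All rescued pregnancies born then (f = 100%) | 1.54 | 1.00 |
| Other 24 to 27 week births also fall 41% (0.05 → 0.0295) | 0.86 | 0.71 |

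For the last row: (0.0295 + 0.0148)/0.9575 = 4.6%, and 4.6/5.4 = 0.86; all randomised, (0.0443 + 0.0425)/0.122 = 0.71. With that 41% fall, the planned ratio is back above 1 if every rescued pregnancy is born at 24 to 27 weeks (1.14), or if v is 2% with f at 50% (1.29).

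**Ranges, other births unchanged.** Leaving share 50% or 80%, braided loss 9% or 19%, v 2% to 8%:

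- f from 25% to 100%: planned RR 1.04 to 3.83, all-randomised RR 0.73 to 1.00.
- f = 0: planned RR 0.93 to 0.98, all-randomised RR 0.64 to 0.85.

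**The case against.** **Size and direction.** The documents give no gestational distribution, so every figure above rests on assumptions. Background {6a} says the benefit comes from preventing early delivery, so holding other births at 24 to 27 weeks fixed is only one scenario. This stands: reversal is possible, not expected.

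A reader might remove every loss from the denominator and get something more dramatic. Per 1000 women, take 92 v 54 losses, an assumed 27 other live births before 28 weeks in each arm, and half of the 38 saved born then: (46/946)/(27/908) = 1.64. That is not the planned analysis. A baby born alive at 24 weeks or later who dies in the first week counts as a pregnancy loss but remains a live birth. If 20% of losses are such deaths after birth at 24 to 27 weeks, the result is (56.8/956.8)/(45.4/926.4) = 1.21.

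**Breadth.** A reader might infer that the randomised comparison is lost for most secondary outcomes. By listed item, 13 carry a live-birth or preterm restriction (one is a near duplicate) and 14 carry none. The 14 are time to pregnancy end, ten maternal items, early and late neonatal death, and neonatal serious adverse events.

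**Intention to treat.** A reader might say that the restriction breaks "All analyses will be by intention to treat". Section {20c} contrasts that principle with as-treated and per-protocol analyses, so it concerns analysis by allocated arm. Choosing a denominator is a separate question, and there is no contradiction.

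**Necessity and existing cover.** Birth weight, length of stay and days of respiratory support exist only for live-born babies. Losses, and time to pregnancy end for any reason, are reported alongside, so a shift in who survives would be visible. Both points stand. But gestation when pregnancy ends exists for every woman, and a hazard ratio does not replace the threshold risks.

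**Conclusion.** The concern holds in limited form. The stated denominators for the 28, 32 and 37 week thresholds, and for the three preterm-only neonatal items, depend on events after randomisation that the suture is expected to change. Those comparisons can be biased. For births before 28 weeks the bias can be large enough to turn a benefit into apparent harm (1.26 planned against 0.88 in all randomised women). Under other reasonable inputs it only weakens the benefit (0.86 against 0.71, or 0.93 to 0.98 planned when no rescued pregnancy is born at 24 to 27 weeks).

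The structural point needs only the listed denominators and the expected effect on loss. The size rests on the assumed leaving share, birth distribution and fate of rescued pregnancies, and on a loss rate back-solved from 2050. No size was calculated for the preterm-only items. The trial's primary conclusion is not touched.

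**What to change.** - **Thresholds.** Add pregnancy ended for any reason before 28, 32 and 37 weeks in all randomised women, analysed like the other binary outcomes, as the main threshold comparison. Keep the live-birth versions as supportive, labelled as conditional on a post-randomisation event.
- **Disabilities and congenital abnormalities.** Report in all live births, not only those before 37 weeks.
- **Oxygen, enterocolitis, retinopathy.** Also give event counts over all randomised women, with term babies counted as unaffected, beside the deaths and losses. Interpret the preterm-only results cautiously.

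There is no need to suppress effect estimates in live births. Nor is there a need to make loss-or-morbidity composites the main neonatal comparison; at about 9% loss these could largely repeat the primary outcome.

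The cost is a few extra analyses. The timing of pregnancy end is already needed for the key secondary outcome, so the thresholds need no new data. The article does not show whether the baby form records disabilities and congenital abnormalities at term, so that should be checked. Recruitment is complete, so the change should be documented before the final analysis.
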